### Assignment and randomisation

Patients who have been screened and deemed eligible will be included in the trial following the provision of written informed consent. Randomisation will be conducted intraoperatively, after the completion of the oesophagogastrostomy and verification of the exclusion criteria. The randomisation lists were generated by block randomisation (block size 10) by a computer-based random number generator using the R statistical package (version 4.4.1). The lists were incorporated into the REDCap randomisation tool. The randomisation process will be conducted by authorised trial personnel using the electronic REDCap system.

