### Trial visits

A total of four trial visits will be conducted throughout the course of the trial. During the initial screening visit (visit 1), inclusion criteria and two out of four exclusion criteria will be evaluated. Once the patient has provided informed consent, the following patient characteristics are documented: basic demographic data, comorbidities, the modified frailty index (mFI), American Society of Anesthesiologists (ASA) and Eastern Cooperative Oncology Group (ECOG) scores, as well as tumour-specific parameters. Furthermore, patients are required to complete questionnaires assessing their preoperative quality of life. Quality of life will be evaluated using the aforementioned EORTC questionnaires, depending on the tumour localisation.

The second visit (visit 2) is scheduled for the day of surgery. Once the oesophagogastrostomy has been completed and none of the remaining two exclusion criteria (conversion and malfunction of the stapler) applies, the patient will be randomised using the REDCap randomisation tool. Intraoperative parameters will be collected, including incision-to-suture time, additional suture time for the anastomosis (study arm B), characteristics of the used stapler and intraoperative transfusions of packed red blood cells. Furthermore, the surgeon’s subjective intuition (subjective risk assessment) regarding four postoperative complications (anastomotic leak, conduit necrosis, chyle leak and recurrent laryngeal nerve injury/palsy) will be assessed.

The third and fourth study visits (visit 3 = 30 days postoperative and visit 4 = 6 months postoperative) may be conducted either as part of standard follow-up visits or by telephone. Visit 4 is considered to be part of the standard oncological follow-up. This encompasses a CT scan of the thorax and abdomen, in addition to an esophagogastroduodenoscopy, should clinical symptoms of dysphagia be observed. The primary and secondary endpoints, along with any serious adverse events (SAEs and AEs), will be evaluated and documented during each visit on the case report form (CRF). Data from patients with stapler malfunction, conversion to open surgery or inoperability will be documented until the time of the operation (visit 2). During visits 1 and 4, the standard blood tests (including haemoglobin concentration, leucocyte count and serum C-reactive protein) will be carried out and documented.

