### Statistics

#### Statistical considerations

All analyses will be performed on an intention-to-treat basis, which comprises all patients randomised with successful RAMIE. Discrete endpoints including the primary endpoint will be described with the use of frequencies and percentages with 95% confidence intervals and will be compared by the chi-square test or Fisher’s exact test. Although randomisation is expected to balance baseline characteristics, additional multivariate analysis will be performed for variables affecting binomial endpoints to control for potential residual confounding. This analysis will use a multivariable logistic regression model including clinically relevant covariates that may influence anastomotic healing. These variables include, but are not limited to age, body mass index (BMI), tumour histology, neoadjuvant treatment and stapler diameter. Adjusted odds ratios (ORs) with 95% confidence intervals will be reported.

Continuous outcomes such as incision-to-suture time will be compared between groups using either Student’s *t*-test (if normally distributed) or the Mann–Whitney *U* test (if skewed). Ordinal outcomes, such as the Clavien–Dindo complication grading, will be analysed with non-parametric tests like the Mann–Whitney *U* test.

Quality-of-life scores obtained from the EORTC QLQ-C30, QLQ-OES18 and QLQ-OG25 questionnaires at baseline and 6 months postoperatively will be assessed using repeated measures analysis, such as mixed-effects linear models, to account for within-subject correlation over time. For any time-to-event outcomes (e.g. time to readmission or death), Kaplan–Meier survival analysis and the log-rank test will be applied, and, if appropriate, a Cox proportional hazards model will be used to estimate hazard ratios with 95% confidence intervals.

All statistical tests will be two-sided, with a significance level set at *α* = 0.05. Sensitivity analyses will be performed using the per-protocol population. All analyses will be fully specified in a statistical analysis plan that is written prior to database closure.

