#### Sample size calculation

Despite an extensive literature search, no studies could be found comparing oesophagogastric anastomosis using a circular-stapled, end-to-side technique with circumferential suture reinforcement in a minimally invasive setting. Due to the lack of reliable data to calculate the sample size at the time of study preparation, an adaptive sample size design was chosen. A total of 100 patients (50 per arm) will be enrolled initially, with the option to adjust the sample size, if necessary. After enrolment of the first 100 patients, an interim analysis is planned to determine the final sample size. The criteria for the continuation of the study are an absolute difference in the primary endpoint of at least 1% to justify the clinical relevance of the study and a calculated sample size of a maximum of 1000 patients per arm to ensure the feasibility of the study.

Although robust prospective data comparing circular-stapled oesophagogastric anastomosis with and without circumferential suture reinforcement in RAMIE are lacking, a preliminary power calculation was performed based on current literature to justify the adaptive design and interim analysis. International multi-centre registry data on RAMIE procedures report an anastomotic leakage rate of approximately 17% for circular-stapled anastomoses without additional suture reinforcement [8]. In contrast, a large retrospective propensity score-matched analysis by Tu et al. [17] demonstrated a significant reduction in leakage rates from 10.3% to 4.7% following circumferential suture reinforcement in circular-stapled anastomoses during McKeown oesophagectomy. Based on these findings, we conservatively assume a reduction from 17 to 11% as clinically meaningful in our study population.

Using these assumptions, a two-group chi-squared test with a significance level of 0.05 (two-sided) and a power of 80% yields a required sample size of approximately 525 patients per arm to detect a difference of 6 percentage points. This supports the current design’s feasibility boundary of up to 1000 patients per arm and justifies continuation after interim analysis if the observed difference in leakage rates exceeds 1%. Moreover, in case of early evidence for superiority (i.e. absolute difference ≥ 5% with *p* < 0.01 in the primary endpoint), the study may be terminated early upon recommendation by the steering committee.

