#### Data collection

To achieve study results that are comparable to those of other trials regarding oesophagectomy, the assessment of postoperative morbidity in the STITCHES trial is based on the recommendations of the Esophagectomy Complication Consensus Group (ECCG) [8]. During each study visit, all parameters of interest, including primary and secondary endpoints and AEs/SAEs, are evaluated and documented in accordance with the standardised eCRF.

Visit 1: The following patient characteristics are documented: basic demographic data (age, sex, height, weight and BMI), mFI, ASA and ECOG scores, as well as tumour-specific parameters (tumour type and location, TNM classification, and the prevalence and type of neoadjuvant treatment). A preoperative blood test is conducted including serum albumin, creatinine, haemoglobin, leukocytes, CRP, vitamin B12, vitamin D3 and tumour markers CA 19–9 and CEA. Furthermore, each patient is required to complete the EORTC QoL questionnaires.

Visit 2: On the day of surgery, the incision-to-suture time, duration of additional suture of the anastomosis (if randomised to study arm B), type of stapler (manufacturer, diameter, powered stapler, yes or no) and the number of intraoperative blood transfusions are recorded.

To document the duration of suture reinforcement of the stapled anastomosis, the timer is started with the initial stitch and stopped with the cutting of the suture. Furthermore, a subjective risk assessment is conducted by the surgeon regarding four postoperative complications: anastomotic leak, conduit necrosis, chyle leak and recurrent laryngeal nerve injury/palsy.

Visit 3: This study visit encompasses possible postoperative mortality and morbidity, the necessity for blood transfusions, the date of discharge and the occurrence of readmission to the hospital. The discharge information comprises the location of discharge, whether at home or to a further medical facility. Morbidity is evaluated and documented in accordance with the ECCG criteria and graded according to Clavien–Dindo.

Visit 4: This study visit includes all parameters of visit 3. Furthermore, an oncological follow-up (suspected and/or confirmed relapse), as well as a routine blood test and an assessment of quality-of-life following surgery (corresponding to visit 1) are required.

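### The quality-of-life analysis names neither the arm contrast nor an adjustment for the pre-randomisation baseline; the usual unconstrained repeated-measures form would be unbiased but less precise

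*Protocol article*

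**What the plan says.** Under Statistical considerations, the Protocol article states that scores from the three EORTC instruments "at baseline and 6 months postoperatively will be assessed using repeated measures analysis, such as mixed-effects linear models, to account for within-subject correlation over time". No test contrast, baseline covariate or constraint on the baseline means is named. The same section does list covariates for the binomial endpoints, and it leaves full specification of all analyses to a statistical analysis plan to be written before database closure.

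The timing is clear from other sections. At visit 1 (Trial visits), "patients are required to complete questionnaires assessing their preoperative quality of life". Under Assignment and randomisation, "Randomisation will be conducted intraoperatively, after the completion of the oesophagogastrostomy and verification of the exclusion criteria". At visit 4, six months after surgery, an "assessment of quality-of-life following surgery (corresponding to visit 1) are required" (Data collection). There are thus two scores per patient, and the first precedes allocation.

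Quality of life is a named secondary endpoint. Under Aim of the study, it is one of the outcomes that the intervention is hypothesised to influence. No standard deviation, effect size, correlation or power is given for it.

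**The concern.** Allocation cannot affect a score recorded before it, so the two arms have the same expected baseline mean by design. An analysis can exploit this by conditioning on the baseline score or by forcing the two baseline means to be equal. The protocol sentence does neither explicitly. It lists baseline as one of the repeated values and stops there.

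A statistician who follows that wording with common defaults would fit arm, time and arm-by-time and test the interaction. With two time points and complete data, that is a comparison of mean changes between arms. It estimates a baseline difference known to be zero in expectation and subtracts it in full, so chance baseline imbalance adds noise. What is at stake is precision: wider confidence intervals and lower power than the data already collected allow.

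**Working it through.** **The plan's own figure.** The only sample-size figure is for leakage, not quality of life. The plan says that "we conservatively assume a reduction from 17 to 11% as clinically meaningful in our study population". It uses "a two-group chi-squared test with a significance level of 0.05 (two-sided) and a power of 80" per cent, which "yields a required sample size of approximately 525 patients per arm to detect a difference of 6 percentage points".

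- Mean rate (0.17 + 0.11)/2 = 0.14.
- n = [1.960 × √(2 × 0.14 × 0.86) + 0.842 × √(0.17 × 0.83 + 0.11 × 0.89)]² / 0.06² = 524 per arm.
- Power at 525 per arm is 80.1%.

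The figure reproduces. It says nothing about quality of life and serves below only as a possible trial size.

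**Inputs for quality of life**

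- From the document: two scores per patient, baseline before randomisation, 1:1 allocation. For alpha, "All statistical tests will be two-sided, with a significance level set at" 0.05.
- Assumed, because the document gives no value: equal score variance at both visits, complete data, rho of 0.3, 0.5 or 0.7, and an effect for which the adjusted analysis has 80% power.

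**Variance of the arm contrast**, in units of (score variance) × 2/n, large-sample:

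- Arm-by-time interaction (difference in changes): 2(1 − rho)
- ANCOVA on baseline: 1 − rho²
- Mixed model with a common baseline mean: 1 − rho² (generalised least squares gives 0.91, 0.75 and 0.51 at the three rho values, identical to ANCOVA)
- Unconstrained arm difference at 6 months: 1

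The ratio of adjusted to change-score variance is (1 − rho²)/[2(1 − rho)] = (1 + rho)/2. The difference is 2(1 − rho) − (1 − rho²) = (1 − rho)², which is never negative. Under these assumptions adjustment therefore cannot be less precise.

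**Power.** With z(0.975) + z(0.80) = 1.960 + 0.842 = 2.802, power of the change contrast = Φ(2.802 × √[(1 + rho)/2] − 1.960).

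| rho | Change variance | Adjusted variance | Ratio | Change power | Loss from 80% |
|---|---|---|---|---|---|
| 0.3 | 1.40 | 0.91 | 0.65 | 61.7% | 18.3 points |
| 0.5 | 1.00 | 0.75 | 0.75 | 67.9% | 12.1 points |
| 0.7 | 0.60 | 0.51 | 0.85 | 73.3% | 6.7 points |

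The common-baseline mixed model has the adjusted variance, so its loss is 0 in every row.

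**Sensitivity to the assumptions**

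- If the adjusted analysis has 90% power, the loss for rho 0.3 to 0.7 is 15.7 to 5.2 points.
- Over rho 0.1 to 0.9, from 80%, the loss is 25.3 to 2.0 points.

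**At fixed trial sizes**, with assumed standardised effects (adjusted vs change power):

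| Per arm | Effect | rho 0.3 | rho 0.5 | rho 0.7 |
|---|---|---|---|---|
| 50 | 0.3 SD | 34.9% vs 24.4% | 41.0% vs 32.3% | 55.6% vs 49.1% |
| 525 | 0.2 SD | 92.5% vs 78.2% | 96.3% vs 90.0% | 99.5% vs 98.7% |
| 525 | 0.3 SD | 99.9% vs 98.4% | 100% vs 99.8% | 100% vs 100% |

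The loss matters most if the trial stays near its first 100 patients or the effect is small. It is close to nil at 525 per arm with an effect of 0.3 SD.

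**The case against.** The strongest reply is that the protocol does not choose the inefficient contrast. It offers mixed-effects linear models as an example of repeated-measures analysis. A mixed model with baseline among the outcomes and one common baseline mean is exactly such an analysis and matches ANCOVA in precision. Model terms and the tested contrast for a secondary endpoint are also ordinary SAP content, and the protocol defers to an SAP that is not shown. Both points stand. They rule out the reading that treating baseline as a repeated outcome in itself costs power, and the reading that a loss of 7 to 18 points is a stated property of the plan.

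A reader might also infer that the arm main effect, averaged over both visits, will be reported. That would halve a 6-month effect and, on the same assumptions, leave about 38%, 29% or 19% power at rho 0.3, 0.5 or 0.7. Nothing in the document suggests that this contrast is intended.

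Nor is there a validity problem. The arm-by-time contrast is unbiased under randomisation, and chance baseline imbalance is part of the sampling variance that its confidence interval already covers.

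The deferral does not dispose of the point altogether. The published sentence describes baseline as a repeated value and mentions no adjustment, so the common default implementation is the less precise one.

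**Conclusion.** The point holds as a minor, conditional matter of efficiency on a secondary endpoint for which the trial is not sized. The wording leaves the arm contrast open and makes no stated use of the fact that baseline precedes randomisation. If the unconstrained arm-by-time contrast is used, power falls from 80% to about 62%, 68% or 73% for rho 0.3, 0.5 or 0.7. These figures assume equal variances, complete data, those values of rho and the 80% reference, none of which the document gives. If a common baseline mean or baseline adjustment is used, nothing is lost. No stated figure is wrong and no bias arises.

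**What to change.** State in the SAP, and in the protocol at the next amendment, that the quality-of-life treatment effect is the arm difference at 6 months, estimated in one of two ways:

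- by a mixed model for the baseline and 6-month scores with the baseline mean constrained equal across arms (terms: time and arm-by-6-months, no arm main effect); or
- by ANCOVA of the 6-month score on baseline score and arm.

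Name one of them as the analysis. They have the same efficiency with complete data but are not interchangeable when scores are missing. Complete-case ANCOVA drops patients who have only one of the two scores, while the constrained mixed model keeps them.

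The cost is a sentence of model wording. No extra data, visits or patients are needed, and the SAP is in any case due before database closure.

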## Background

In the modern multimodality treatment of oesophageal cancer, oesophagectomy has a fundamental role. However, due to its complexity and invasiveness, it is defined as a high-risk procedure that is associated with a higher morbidity than most other surgical procedures. In Germany, a population-based observational study using administrative data found a nationwide caseload-related in-hospital mortality rate ranging between 12.3% (95% confidence interval: 11.1–13.7) and 20.0% (18.5–21.6) [13]. Recent studies have shown a significant improvement in perioperative outcomes with minimally invasive approaches [11]. As a result, the German guideline for oesophageal cancer from the German Guideline Program in Oncology (GGPO) recommends the use of minimally invasive oesophagectomy (MIE) [5]. Robot-assisted minimally invasive oesophagectomy (RAMIE) is a technical advancement that may lead to further improvements in patient outcomes. Compared with MIE, RAMIE can achieve shorter operative times and better lymph node yield in patients who have received neoadjuvant therapy [18].

Irrespective of the type of surgical approach, the formation of the oesophagogastric anastomosis is critical to the success of the operation, as an anastomotic leakage is associated with significant morbidity and mortality [13, 15]. In Ivor-Lewis RAMIE, three distinct anastomotic techniques are currently in use [15]. The anastomosis can be sutured by hand, stapled in a linear fashion side to side, or in a circular fashion end to side. A recent analysis of a multi-centre international registry on RAMIE revealed that the circular-stapled anastomotic technique is employed in 52% of cases, in comparison to 30% for hand-sewn and 18% for linear stapled anastomotic techniques [8]. The highest anastomotic leakage rate was observed in the robot-assisted hand-sewing group (33%), while lower rates were noted in the circular stapling (17%) and linear stapling (15%) groups. These relatively high rates are in contrast with the average incidence of anastomotic leakage of 6.2% reported in a meta-analysis comparing RAMIE with open oesophagectomy [6].

In order to reduce the incidence of anastomotic leakage, different techniques of anastomotic reinforcement have been proposed in the past, including the use of tissue sealant, omental flap and additional suture reinforcement [2, 16, 17].

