#### Secondary endpoints

Secondary endpoints include incision-to-suture time, duration of circumferential suture reinforcement, anastomotic stenosis rate, postoperative morbidity and mortality according to the Clavien–Dindo classification (CDC), and quality of life. Perioperative complications associated with oesophagectomy are recorded in accordance with the ECCG definitions.

Postoperative morbidity with CDC grade ≥ 3b will be the secondary safety endpoint. Quality of life (QoL) is assessed using the EORTC QLQ-C30, EORTC QLQ-OES18 and EORTC QLQ-OG25 questionnaires [1, 3, 9], provided by the European Organisation for Research and Treatment of Cancer.

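### Kaplan–Meier is named for time to readmission with no provision for death as a competing event, so 1 minus KM from surgery would slightly overstate the proportion readmitted in each arm

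*Protocol article*

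**What the plan says.** The protocol article, Statistical considerations, sets one rule for all time-to-event outcomes: "For any time-to-event outcomes (e.g. time to readmission or death), Kaplan–Meier survival analysis and the log-rank test will be applied". A Cox model is conditional: "if appropriate, a Cox proportional hazards model will be used to estimate hazard ratios with 95% confidence intervals". The section does not mention competing risks or cumulative incidence, and does not say how a death before readmission is treated or when time starts. It refers detail to a later document: "All analyses will be fully specified in a statistical analysis plan that is written prior to database closure".

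Readmission is collected. Under Data collection, visit 3 covers mortality and, as separate items, "the date of discharge and the occurrence of readmission to the hospital"; visit 4 repeats these. The visits are placed at "visit 3 = 30 days postoperative and visit 4 = 6 months postoperative". Readmission is not among the Secondary endpoints, which do include "postoperative morbidity and mortality according to the Clavien–Dindo classification (CDC), and quality of life".

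On mortality, the Background cites nationwide German in-hospital figures of 12.3% to 20.0%, and the Discussion cites up to 28% after a leak. Neither is a planning assumption of the trial.

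**The concern.** Kaplan–Meier treats a censored patient as someone who could still have the event later. For readmission alone, a patient who dies first is censored, yet can no longer be readmitted; one who dies before discharge was never able to be. The curve then estimates what would be seen if nobody died, and 1 minus KM lies above the share of operated patients who are readmitted.

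The sentence is mandatory in form and gives readmission as an example, so an analysis plan that follows it takes over the method. At stake is the absolute readmission curve in each arm, in an operation where early death is not rare.

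**Working it through.** **The plan's own figure.** The article gives no number for readmission. Its one computed figure is about 525 per arm for 17% versus 11% (two-sided 0.05, 80% power). The pooled chi-square formula gives (1.960 × √(2 × 0.14 × 0.86) + 0.842 × √(0.17 × 0.83 + 0.11 × 0.89))² / 0.06² = 524, so it reproduces. It is used below only to scale standard errors.

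**Inputs.**
- Mortality: 12.3% and 20.0% from the Background; 2–5% assumed as a lower range.
- Readmission risk by 6 months: not in the article; assumed 10–30%, with 20% as the central value.

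**Calculation A: constant hazards over 6 months.** Let R be the true cumulative incidence of readmission and D that of death before readmission.
- Total hazard = −ln(1 − R − D).
- Readmission hazard = total × R / (R + D).
- 1 − KM = 1 − exp(−readmission hazard).

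For R = 20% and D = 12.3%, the total is −ln(0.677) = 0.390, the readmission share is 0.390 × 0.20 / 0.323 = 0.2415, and 1 − KM = 21.5%. The excess is 1.5 points. A simulation of 400,000 patients gave 21.5% against a true 20.0%.

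| D | Excess at R = 10% | R = 20% | R = 30% |
|---|---|---|---|
| 2% | 0.1 | 0.2 | 0.3 |
| 5% | 0.3 | 0.6 | 0.9 |
| 12.3% | 0.7 | 1.5 | 2.3 |
| 20% | 1.2 | 2.5 | 4.0 |

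**Calculation B: early deaths.** In-hospital deaths precede any readmission of those patients, so constant hazards understate the effect. Simulation with deaths on days 1–30, readmissions on days 14–180, and the readmission risk r applied to the patients who do not die early gave:

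| Mortality | Excess at r = 10% | r = 20% | r = 30% |
|---|---|---|---|
| 3% | 0.3 | 0.6 | 0.9 |
| 5% | 0.5 | 0.9 | 1.5 |
| 12.3% | 1.2 | 2.4 | 3.6 |
| 20% | 2.0 | 3.9 | 5.9 |

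Hand check at 12.3% and r = 20%: true incidence is 0.877 × 20% = 17.5%. If all deaths came first, 1 − KM would be 20%, an excess of about 2.5 points, close to the simulated 2.4.

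**Scale.** The standard error of one arm's proportion at 525 per arm is √(0.20 × 0.80 / 525) = 1.7 points. An excess of 1.5 to 2.4 points is therefore about 0.8 to 1.4 single-arm standard errors.

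**Difference between arms.** With early deaths, the excess in an arm is close to r × D, so the differential excess is r × (difference in D). Suppose every prevented leak carried the full 28% mortality. The mortality difference is then at most 0.06 × 0.28 = 1.7 points, and the differential excess is 0.20 × 1.7 = 0.3 points. The standard error of the arm difference is √2 × 1.7 ≈ 2.5 points, so this is about 0.14 standard errors. Even with deaths at 12.3% versus 8%, a wider gap than those figures support, equal readmission hazards (1 − KM of 20% in both arms) correspond to true incidences of 18.6% and 19.1%, a difference of 0.5 points.

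**The case against.** **Deferral to the analysis plan.** Time origin and censoring rules are ordinary analysis-plan content, and the article never says that deaths are censored. That stands for the detail. It does not remove the point, because the article already fixes the estimator, and Kaplan–Meier for readmission alone has no other way to treat a prior death.

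**Composite reading.** The bracketed example can be read as one event, readmission or death, for which Kaplan–Meier is correct. This reading is open. Two separate examples is the more natural sense, and separate recording at visit 3 fits it, but a composite is also built from separately recorded parts. The text does not settle it.

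**Time from discharge.** If time started at discharge, in-hospital deaths would never enter the risk set and most of the excess would vanish. That is true, but it conditions on surviving to discharge, which happens after randomisation and may differ by arm, and it leaves the randomised population on which the article bases its analyses. The article states no time origin.

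**A simple percentage may be reported instead.** Discrete endpoints are to be given as frequencies and percentages, and readmission is recorded as an occurrence. A plain percentage does not have this bias. The point therefore bites only where the curve is read as a proportion.

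**Log-rank and Cox.** A reader might infer that these are invalid. They are not: with deaths censored, both compare cause-specific hazards correctly, and Cox applies only where appropriate. Gray's test answers a different question, and preferring it is a choice of estimand.

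**Conclusion.** The point holds as a minor one. On the two-outcome reading, with time from surgery, 1 minus KM overstates the proportion readmitted in each arm. The direction is certain; the size rests on assumed readmission risks. It is roughly 0.3 to 1.5 points at 3–5% mortality (early-death timing, readmission 10–30%), and about 1.5 to 2.4 points at 12.3% mortality with about 20% readmission. The lower of those last two values is for constant hazards, the upper for early deaths.

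Two stronger readings are tempting and not supported. The first is that the comparison between arms is materially distorted: on the article's own leakage and mortality figures the differential is about 0.3 points. The second is that the upper background mortality of 20.0%, with an excess of 2.5 to 3.9 points at 20% readmission, describes this trial. Both background mortality figures are nationwide values, whereas the trial enrols elective robot-assisted cases operated on by surgeons with a minimum experience, so the lower mortality range may be nearer.

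Readmission is not a listed endpoint. The primary result and the sample size do not depend on any of this.

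**What to change.** In Statistical considerations, and in the analysis plan that follows it:
- Keep Kaplan–Meier, log-rank and Cox for time to death, or for a composite of readmission or death if that is what is meant, and say which.
- For readmission alone, report the Aalen–Johansen cumulative incidence from surgery with death as a competing event.
- Label any log-rank or Cox result for readmission as cause-specific. Gray's test is optional.

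The cost is one or two sentences. The dates required are those that any time-to-event analysis of readmission and death already needs. The only downside is that reported readmission rates come out slightly lower. The analysis plan is due before database closure and recruitment is anticipated to run to October 2026, so the change can still be prespecified.
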